#### Aim 2 statistical methods

*RQ5 and RQ6*. Structural equation modeling (SEM) will be used to investigate the structural relationship between the measured behavior change techniques, latent behavior change mechanisms and youth outcomes.

#### Aim 3 statistical methods

*RQ7*. Fidelity ratings from the systematic session observation at T2 will be compared across My Choice–My Way! groups to investigate differences in implementation quality (e.g., independent samples t-test, Mann-Whitney U depending on final data characteristics).

*RQ8*. Fidelity measures collected from My Choice–My Way! T3 will be compared (e.g., ANOVA) for significant differences between groups.

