### Objectives

The purpose of this project is to increase our understanding of how to promote the well-being across a spectrum of outcome areas for youth (15 + years old) transitioning from out-of-home care to independent living through the study of the implementation and provision of (A) My Choice—My Way! (*Swe*. Mitt val–min väg!) and (B) Usual Services. This includes an increased understanding of how interventions for this population can be designed, implemented, and sustained in diverse settings.

The project has five specific aims and eleven research questions.

#### Aim 1

To test the short- and sustained effectiveness of My Choice-My Way! in normal practice settings.

H1: Youth participating in My Choice-My Way! will exhibit gains in well-being and psychosocial outcomes relative to youth participating in Usual Services.

*Research questions*. RQ1 What is the relative effectiveness of My Choice-My Way! and Usual Services (US) for youth aged 15 and older in out-of-home care on well-being and psychosocial outcomes?

RQ2 How are outcomes moderated by subgroup characteristics?

RQ3 How does implementation fidelity moderate outcomes?

RQ4 What is the relative economic impact of My Choice–My Way!?

#### Aim 2

To advance our understanding of how specific behavior change techniques and theory-based change mechanisms impact youth outcomes.

H2: Theoretically based change mechanisms (e.g., experiences of success targeting self-efficacy change) will have a mediating effect on outcome (e.g., increased engagement in educational activities) in interventions with detailed program content.

*Research questions*. RQ5 How are the specific behavior change techniques used by social workers related to theoretical change mechanisms?

RQ6 How do the specific change mechanisms in transition services mediate youth outcomes?

#### Aim 3

To assess the extent to which implementation support (i.e., GTO) can impact fidelity and sustainability in practice settings.

H3: Organizations engaging in implementation support will exhibit increased fidelity relative organizations not engaging in implementation support.H4: Organizations engaging in implementation support will exhibit increased sustainability relative organizations not engaging in implementation support.

*Research questions*. RQ7 How does implementation support impact fidelity?

RQ8 How does implementation support impact sustainability?

#### Aim 4

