### Trial design

The study can be described as a hybrid effectiveness-implementation study with natural controls in a quasi-experimental two-arm study design [30]. We will conduct such a study to test the impact of the leaving care interventions while we at the same time collect data on the implementation process and outcomes (i.e., Hybrid I design). Research design and methods for data analysis specifically linked to each of the aims and research questions will be described in more detail below.

#### Design Aim 1

We will perform an effectiveness study to achieve Aim 1 and to answer RQ1-RQ4. The effectiveness study will be carried out as a natural quasi-experiment with two groups of youth participants (My Choice–My Way!, US) with dependent pre-, post- and follow-up measures [31] (i.e., 3 x 3 mixed factorial design. Long-term outcomes will be studied with a longitudinal register study.

#### Design Aim 2

Based on the My Choice–My Way! theory of change (i.e., logic model, [32]) salient change mechanisms will be chosen and measured.

#### Design Aim 3

Posttest comparison study comparing implementation and youth level outcomes for organizations engaged in implementation support with organizations not receiving implementation support.

#### Design Aim 4

Qualitative implementation, posttest interview study with service providers.

#### Design Aim 5

Qualitative implementation, posttest interview study with youth participants.

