### Study setting

This is a multicenter research project that will be conducted at a total of 21 research sites throughout Sweden. Organizations have naturally self-selected to either implement My Choice–My way! (*n* = 12) or to continue providing Usual Services (US, *n* = 9). All twelve organizations that implement My Choice—My Way! are part of the Swedish social services, although some are public and others private providers of services to youth. The nine organizations that constitute the control group and provide US are various organizations that provide support for the target group either within the Swedish social services or as a part of civil society. A list of study sites can be obtained from the first author of this protocol.

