#### Systematic session observation

Two sessions per youth will be randomly selected in the My Choice-My Way! arm of the study. The service provider will make a video recording of themselves (i.e., no video recordings of youth participants) providing the session to participant youth. The recordings will be sent to the research team for analysis of fidelity to model based on a structured assessment instrument.

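### H3 and H4 are about organisations, but the tests named for RQ7 and RQ8 need independent observations and the plan does not fix the organisation as the unit; if ratings or youth are the unit, the 5% error rate does not hold

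*Protocol article*

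**What the plan says.** Under Objectives, H3 reads "Organizations engaging in implementation support will exhibit increased fidelity relative organizations not engaging in implementation support" and H4 reads "Organizations engaging in implementation support will exhibit increased sustainability relative organizations not engaging in implementation support". The Trial design section (Design Aim 3) keeps that level: it compares "organizations engaged in implementation support with organizations not receiving implementation support".

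The Study setting section lists 12 organisations delivering My Choice–My Way!. Fidelity is observed only in that arm. Under Systematic session observation, "Two sessions per youth will be randomly selected", and the service provider records them.

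Under Aim 3 statistical methods, RQ7 compares the fidelity ratings from these observations across My Choice–My Way! groups. The example methods are "independent samples t-test, Mann-Whitney U depending on final data characteristics". For RQ8, fidelity measures from T3 "will be compared (e.g., ANOVA) for significant differences between groups".

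Nothing in the article mentions clustering, a random effect, an intraclass correlation (ICC) or averaging to the organisation. It also does not say how many organisations receive GTO or how that support is allocated.

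**The concern.** Support is received by the organisation. The ratings lie lower down: sessions within youth, youth within the provider whose conduct is rated, and providers within the organisation. Ratings from one provider or one organisation can be expected to resemble each other. A t-test, Mann-Whitney U or ANOVA on ratings or on youth would treat them as independent, although at most 12 units carry the GTO contrast. P-values would then be too small and confidence intervals too narrow, and ordinary differences between organisations could be reported as an effect of GTO.

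These are the only two hypotheses under Aim 3, and the Project novelty section presents the test of implementation support as a main contribution. The issue is separate from the My Choice–My Way! versus Usual Services comparison. The exposure, the outcome and the set of organisations all differ, so a change to the RQ1 model would leave RQ7 and RQ8 as they are.

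**Working it through.** **Plan's own figure.** There is none for RQ7 or RQ8. The Sample size section concerns RQ1 only; it is used here for the number of youth.

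**Inputs from the article**
- 12 My Choice–My Way! organisations (Study setting).
- 80 youth recruited per arm; 124 completers in all, so 124/2 = 62 per arm (Sample size).
- 2 rated sessions per youth (Systematic session observation), so 80 × 2 = 160 ratings, or 62 × 2 = 124.

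**Assumptions, because the article gives no figure**
- GTO split 6 v 6 or 3 v 9.
- Youth spread evenly over organisations, 2 youth per provider.
- Organisation ICC (share of rating variance between organisations) from 0 to 0.20.
- Two-sided test at 0.05.

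**Step 1. Design effect, organisation clustering only.** With m ratings per organisation, DE = 1 + (m − 1) × ICC, and the actual error rate is 2 × [1 − Φ(1.96/√DE)].

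For 160 ratings, m = 160/12 = 13.33. At ICC 0.05, DE = 1 + 12.33 × 0.05 = 1.62, 1.96/√1.62 = 1.54, and the error rate is 0.123. For 124 ratings, m = 124/12 = 10.33.

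| Organisation ICC | DE (m = 13.33) | Error rate | DE (m = 10.33) | Error rate |
|---|---|---|---|---|
| 0.01 | 1.12 | 0.064 | 1.09 | 0.061 |
| 0.05 | 1.62 | 0.123 | 1.47 | 0.106 |
| 0.10 | 2.23 | 0.190 | 1.93 | 0.159 |
| 0.20 | 3.47 | 0.292 | 2.87 | 0.247 |

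**Step 2. Simulation with no GTO effect** (8,000 runs per scenario; ranges cover 62 and 80 youth and both splits).

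| Organisation ICC | t-test on ratings | t-test on ratings, plus 10% provider and 10% youth variance |
|---|---|---|
| 0 | 0.045–0.053 | not run |
| 0.01 | 0.057–0.062 | not run |
| 0.05 | 0.105–0.124 | 0.149–0.169 |
| 0.10 | 0.161–0.198 | 0.194–0.233 |
| 0.20 | 0.249–0.307 | 0.284–0.329 |

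Mann-Whitney U on ratings, with organisation clustering only, gives 0.104–0.121, 0.153–0.194 and 0.243–0.292 at ICC 0.05, 0.10 and 0.20. One mean per youth does not cure the problem: the t-test still gives about 0.10–0.12, 0.14–0.18 and 0.20–0.26. A two-group ANOVA is equivalent to the t-test.

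**Step 3. Organisation as the unit.** A t-test on the 12 organisation means gives 0.043–0.052 in every scenario.

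**Step 4. What can be detected.** By the noncentral t with 80% power, the detectable difference is about 1.8 SD of organisation means at 6 v 6 and about 2.1 at 3 v 9. With organisation clustering only and 160 ratings, the SD of an organisation mean is √[ICC + (1 − ICC)/13.33] rating SDs. At ICC 0.05 this is √(0.050 + 0.071) = 0.35, so the detectable difference at 6 v 6 is 1.8 × 0.35 = 0.63 rating SD. At ICC 0.20 it is √(0.20 + 0.06) = 0.51, and 1.8 × 0.51 = 0.92. A test of 80 v 80 ratings taken as independent would appear able to detect 0.45 rating SD.

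**The case against.** The strongest reply is that the article never states the unit. The hypotheses and the Aim 3 design speak of organisations, and a t-test or Mann-Whitney U on organisation scores would agree with them and be valid; Step 3 confirms this. The methods are also introduced as examples, the article is condensed, and a fuller analysis plan may settle the matter. Aim 3 is not the primary aim.

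Part of this stands. A reader might infer that the plan commits to counting some 160 ratings as independent evidence. The text does not say so; it is the natural reading of a comparison of fidelity ratings, not an explicit rule. A reader might also infer that false positives will be far above 5% whatever the data look like. That is not supported either: at an organisation ICC of 0.01 with no other clustering, the rate is about 6%. Nor can the same inflation be asserted outright for RQ8, because the article does not say what is rated at T3, by whom, or how many ratings there will be.

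What does not stand is that the example wording or an unseen plan removes the point. Every method named needs independent observations. The choice left to the data under RQ7 reads as parametric versus rank-based, and neither handles nesting. A team could run the test on ratings and still comply with the published text.

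**Conclusion.** The point holds in conditional form. The hypotheses are set at organisation level, the data lie below it, and the named tests are valid for these hypotheses only if the organisation is the unit, which the plan does not secure.

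If ratings are the unit for RQ7, the false-positive rate is about 6% at organisation ICC 0.01 alone, 10–12% at 0.05, 16–20% at 0.10 and 25–31% at 0.20. It is higher when provider and youth clustering are added, and averaging to one score per youth removes little of it. These figures rest on assumed ICCs, GTO splits and provider numbers. For RQ8 the conclusion applies only if T3 fidelity is measured at session, youth or provider level. The wording should be changed, but it does not by itself show that the eventual analysis will be invalid.

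**What to change.** Under Aim 3 statistical methods, name the organisation as the unit for RQ7 and RQ8 and choose one of two analyses:

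- One fidelity score per organisation (at most 12), compared by a t-test or an exact permutation test.
- A mixed model on the ratings with random organisation, provider and youth effects and small-sample degrees of freedom.

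State what is measured for fidelity at T3 and at which level. Give the number of supported and unsupported organisations, and report the difference with its confidence interval and the difference detectable at that split. Word the result as an association unless support was randomly assigned; the article does not describe how it was allocated.

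This changes analysis wording only and needs no new data. The cost is wider intervals and an openly modest ability to confirm H3 and H4: about 1.8 SD of organisation means at 6 v 6, and more at an uneven split.

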#### Aim 4 statistical methods

*RQ9 and RQ10*. Service provider interview data will be analyzed with a thematic analysis approach as described by Braun and Clarke [56].

#### Aim 5 statistical methods

*RQ11*. Client satisfaction data collected from youth during T2 data collection will be analyzed with descriptive statistics (e.g., % of participant youth with a given opinion of the support they received). Youth interview data will be used to contextualize and gain further understanding of the perspectives captured in the client satisfaction survey via thematic analysis.

## Discussion

Supporting vulnerable youth in their healthy development is a complex endeavor. This project integrates several scientific fields including social work, developmental psychology, and implementation and intervention science and merges these scientific fields with practitioner expertise to meet this challenge. This research project provides the opportunity to increase scholarship around how we might design interventions for this population specifically and implement services in practice settings specifically but also increase our general scientific knowledge across a range of areas important for the scientific development of intervention and implementation science by attending to a range of areas for which the current scholarship is lacking (e.g., strong research design, mediation and moderation analyses). In addition, this research has an ambitious data collection and analysis strategy which incorporates, qualitative, quantitative and observational data across intervention and implementation in order to support analyses that are exploratory, descriptive and explanatory in nature thereby increasing our ability to study multiple processes and their interaction within the same trial. Importantly, the proposed research project is part of a larger programmatic line of basic and applied scientific work being conducting by our research team with the aim to advance the well-being and psychosocial outcomes of youth transitioning from out-of-home care to independent living.

A main goal of the current research program is to provide social service agencies in Sweden with an effective and feasible intervention that targets youth transitioning between out-of-home care and independent living that can be sustainable over time. To date, such interventions are lacking in the scientific literature. Thus, the research project has in its design to produce knowledge and tools, related to both methods and sustainable implementation, which can be of direct practical use in society. In fact, sustainable use of the intervention in regular services is one of our research questions. We bridge the gap between research and practice via close collaboration with practitioners from social service organizations throughout the project period. The intervention and the implementation strategies will be developed together with the practitioners and will be informed by what matters in “the real world”. Thus, the results of the study will be very useful for the social services in all municipalities in Sweden.

My Choice–My Way! Is the result of an extensive development process which included attention to culture in the early development phase. Cultural fit is key to intervention success [57, 58] but there remains debate in the extant literature on whether this fit should be managed through the cultural adaptation of existing interventions to new context or whether fidelity should be seen as paramount [59]. In addition, a large proportion of interventions are developed in the settings in which they will be used [59, 60]. The current research may be able to contribute to this scholarship in that we test the intervention My Choice–My Way! in the context in which it was developed as well as implement it more widely across social service settings in the same trial.

Our development process was guided by a partnership approach which is described as a collaboration in which researchers and stakeholders work together on a research project with the aim of creating collaborations in which researchers and stakeholders co-lead research activities and collectively apply their expertise, knowledge, and skills within the team [61]. Through this approach we developed an intervention that weaves together scientific theory, implementation best practices and insights from evidence-based practices [62] and as such we believe that the resulting intervention My Choice–My Way! with its theoretical basis in self-determination theory [33], Social Cognitive Theory [34], and the COM-B Model for Behavior Change [18], is highly interesting and promising given that Swedish youth placed in out-of-home care view themselves as not possessing the essential resources and capabilities required to tackle the challenges that arise during the transition from such care [57].

### Gender and diversity perspectives

Even if this project does not directly address gender or diversity as core issues, such issues are essential to intervention and implementation research. In terms of gender, it has been shown that, although more boys are placed in out-of-home care, girls placed in out-of-home care in Sweden are a more adverse and vulnerable group than boys. Important gender differences will be consistently woven into this project and subgroup analyses will include attention to gender. Reporting of results and dissemination will highlight any identified gender issues. Previous research has made clear that the cumulative effects of disadvantage for adolescents in out-of-home care may impact girls and boys differently and the mechanism through which this disadvantage operates appears to be through school achievement. Additionally, girls and boys may accept intervention unequally and access/participate in intervention components unequally. Therefore, this project will keep a strong focus on sex and gender differences and subgroup analyses will be performed.
